### Study site and population

The study is planned to take place in two areas located in the center of Gabon: Lambaréné including vicinities (Bindo, Makouké and Nzilé-PK villages) and Fougamou. Both regions are endemic for *S. haematobium* with the prevalence ranging from 7 to 75%, depending on the area or the population age group [32, 44–46]. The study population are pregnant women and their newborns.

### Ethical considerations

The study protocol and informed consent forms (ICF) were approved by the National Ethics Committee of Gabon (PROT N°039/2018/SG/CNE) and by the Institutional Ethics Committee at CERMEL/Gabon (N° 017/2018). Written informed consent will be sought from any volunteer or the legal guardian of minor volunteers before any study procedure will be performed.

### Recruitment of participants, data and sample collection

Prior to enrolment, the study will be explained to the pregnant women – and legal guardian if minor - presenting to the antenatal care centres (ANC) in Lambaréné (Albert Schweitzer and Regional Georges Rawiri Hospitals). Those willing to participate will be provided with the informed consent form (ICF) for signature for themselves and for their unborn child. Particular emphasis is given to information on *Schistosoma* transmission, diagnosis, associated pathologies and risk factors for *Schistosoma* infection in particular, and to intestinal helminths in general. Inclusion criteria are pregnancy at gestational age between 16 and 30 weeks (based on last date of menses), providing signed ICF, willing to deliver in one of the two maternities in the study areas and no plans to move out of the study area during the following 24 months. Exclusion criteria are reporting of complicated previous pregnancy, known chronic infections or diseases as HIV, HBV, HBC infections. Following the ICF process, a KAP questionnaire will be administered to collect standard demographic, health history, obstetrical data and information on schistosomiasis related knowledge, attitude and practice.. Economic and health-related quality of life (HRQoL) questionnaire will be included as well. The questionnaire will be used to measure HRQoL among all pregnant women at enrollment and to monitor HRQoL among the positive women over time. For this, the HRQoL questionnaire will be administered again to positive women 1 week after enrollment when test results are available and treatment provided (at A4) and a few months later, well after treatment completion (at C2). Physical examination will be done by the study physician; participants will be asked to provide urine (midstream urine will be collected in a clean container), stool and blood samples for parasite diagnostics and health care service. At delivery, newborns will be weighted, and gestation age will be recorded. The newborn’s anthropometry parameters, Apgar score at 1 and 5 min, maternal bleeding volume, placenta quality and weight will be collected. For details on study visits over time with respect to the study phases and details of sample collection see Additional file 1.

### Diagnostics

#### Investigational product: UCP-LF CAA test

The index test is the UCP-LF strip test detecting and quantifying CAA levels. LF strips can be analysed with POC care readers [47] or, as used in this study, with a multistrip benchtop reader (Upcon; Labrox Oy, Turku, Finland) capable of analysing 20 strips at a time. The UCP-LF CAA test was developed at Leiden University Medical Center (Leiden, The Netherlands) [38, 48]. So far, the tests are produced in-house at LUMC in a batch-wise manner (ca. 2000 tests per batch), fully quality-controlled using standardized reference samples, ensuring specificity and sensitivity. A dry reagent format is available that can be stored and transported at ambient temperature [39]. Here, 417 μl of fresh or stored (− 20 °C) urine will be tested by the UCP-LF CAA urine test following published procedures [48] including a concentration step (centrifugal Amicon Ultra 0.5 mL filters with a 10 kD cut-off; Merck Millipore) after pre-treatment of the urine with 1/6 volume of 12% trichloroacetic acid and (UCAA*hT*417 format) [49]. All measurements will include a set of CAA-spiked standards into a negative urine to determine the threshold of positivity that is set to ≥2 pg/ml.

### Comparator diagnostics

#### Urine filtration and egg microscopy

*Schistosoma* egg detection by microscopy is commonly used for the diagnosis of schistosomiasis as recommended by WHO and diagnostic procedures will follow standardized protocols [50]. Urine (10 ml) will be passed through a 12 μm filter (Whatman Nucleopore) using a syringe. The filter will then be placed on a glass slide and read under a light microscopy (10x magnification). Every slide will be read by two independent microscopists. The test will be considered positive if at least one *S. haematobium* egg is found and egg counts will be given (N eggs/10 ml urine).

#### qPCR

*Schistosoma* egg DNA will be detected by real-time PCR (qPCR) on urine samples following a published protocol [51]. We will use the established *Schistosoma* genus-specific primers (Ssp48F and Ssp124R) and the dual labelled probe Ssp78T to amplify a 77-bp fragment of the internal transcribed spacer-2 (ITS2) sub-unit. An internal control will be added to monitor efficient DNA extraction. DNA extraction from urine and qPCR assay will be performed.

#### Serology

Antibodies against *S. haematobium* will be measured using a lateral flow assay (UCP-LF antibody assay) that is based on the same technology as the UCP-LF CAA test and can be evaluated using the same UCP Labrox reader. The serology test is designed to detect antibodies against soluble egg antigen (SEA) and soluble crude cercarial antigen preparation (SCAP) in sera of participants [37, 52].

### Additional diagnostics

#### POC-CCA

The point-of-care (POC) CCA urine test is a commercially available POC rapid test for the detection of CCA in urine (Rapid Medical Diagnostics, South Africa). This LF immuno-chromatography test delivers qualitative detection of active *Schistosoma* infection, and is recommended and generally applied to detect *S. mansoni* infections performing less in *S. haematobium* settings [53, 54]. It is ideally suited for field conditions as it does not require laboratory facilities or highly trained personnel.

### Microscopy for concomitant parasite infections

To control for the impact of concomitant other parasite infections on the accuracy of UCP-LF CAA, stool samples will be investigated for *S. intercalatum* (as well as any other *Schistosoma* species) and for other highly prevalent helminths such as *Ascaris lumbricoides*, *Trichuris trichuria*, Hookworms, and *Strongyloides stercoralis*. Stools will be examined by Kato-Katz and coproculture techniques [53, 55]. Therefore, approximately 50 mg of fresh stool will be processed. Microscopy reading (10x magnification) is done by two independent readers and numbers of eggs per gram of stool will be reported according to WHO guidelines [53, 56]. Remaining stool will be stored for later confirmation by respective qPCR [51]. Blood samples will be examined for infections with malaria parasites (*Plasmodium falciparum*, non-falciparum) and filarial parasites (*Loa loa*, *Mansonella perstans*) by standard diagnostic procedures (Giemsa-stained thick blood smears, saponin leucoconcentration assay followed by microscopy, respectively) [57, 58].

### Treatment, adverse events and safety assessment

Women infected with *Schistosoma* (positive by egg microscopy and/or UCP-LF CAA) will be treated with PZQ either during pregnancy (as recommended by WHO) or after delivery. Single dose PZQ (40 mg/kg) will be administered by an unblinded member of the study team under observation. Safety of PZQ administration in women will be assessed verbally within 24 h (after 1 h and 24 h later) to record all adverse events occurring after drug administration. All adverse events will be assessed by the study physician, following local guidelines and will be graded as mild, moderate or severe. All investigators (study physicians and lab technicians) will be blinded to the treatment allocation. Other parasitic infections will be treated following national treatment guidelines. This work will be done in collaboration with the Gabonese National Program for the Fight against NTDs who will contribute to the PZQ supply.

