**Sub-study B** is an observational, follow-up study of at least 100 pregnant women identified in sub-study A as being infected with *S. haematobium* (by egg microscopy and/or urine UCP-LF CAA test). *Schistosoma*-infected women will be randomised 3:1 (75:25) for immediate PZQ treatment during the pregnancy (single dose of 40 mg/kg) or delayed PZQ treatment after delivery (control group). The control group will not be treated during pregnancy (to monitor “natural” CAA level fluctuation in a participant if not treated), but 6 months after delivery. The primary objective is to determine the kinetics of CAA after treatment during pregnancy compared to the control group. The control group serves also as a safety control of PZQ administration to pregnant women and exposure of their offspring (s). Therefore, both groups (treatment and control) will be actively followed-up and urine will be collected on day 2, day 4 and day 6 after PZQ treatment and then once a week until both egg microscopy as well UCP-LF CAA assay become negative but no longer than 6 weeks after PZQ treatment. The secondary objective is to collect data on safety of PZQ during pregnancy. For details on the safety investigation, see below (treatment, adverse events and safety assessment).

**Sub-study C** will follow up infants born to mothers included in sub-study A and their mothers for a maximum of 24 months (*N* = 200). This is an observational, longitudinal study with the primary objective to determine the incidence of *S. haematobium* infection and age of first *S. haematobium* infection in infants. Therefore, after delivery, mother and her infant will be asked to provide urine every 3 months until the UCP-LF CAA test becomes positive for *S. haematobium* in the infant. Children who test *S. haematobium* positive will be treated with praziquantel according to Gabonese national treatment guidelines.

In addition, a customized questionnaire addressing the knowledge, attitude and practice (KAP) of schistosomiasis of mothers and infants will be asked. Health-related quality of life (HRQoL) will also be measured by using a standardized tool: this will allow filling a wide literature gap, where only very few studies have attempted to measure HRQoL in schistosomiasis endemic areas [43]. To our knowledge, this study will be the first one collecting information on HRQoL among pregnant women in areas endemic of schistosomiasis and of other parasitic infections such as malaria.

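### Maternal adverse events in pregnancy are collected only after PZQ intake, so the control arm gives no concurrent comparison, and the scheme conflicts with the blinding of the assessing physician

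*Protocol article*

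**What the plan says.** Protocol article, Study design, sub-study B paragraph. The safety aim is stated directly: "The secondary objective is to collect data on safety of PZQ during pregnancy". Women are randomised 3:1 (75:25) to immediate or delayed treatment. Of the delayed arm the text says "The control group will not be treated during pregnancy"; these women are treated "but 6 months after delivery". The same arm has a second role: "The control group serves also as a safety control of PZQ administration to pregnant women and exposure of their offspring (s"). Both arms are to be actively followed, with urine collected on days 2, 4 and 6 and then weekly until both tests are negative, for 6 weeks at most. For how safety is investigated, the paragraph sends the reader to the later section on treatment and adverse events.

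That section, Treatment, adverse events and safety assessment, describes the ascertainment: "Safety of PZQ administration in women will be assessed verbally within 24 h (after 1 h and 24 h later"), with the purpose "to record all adverse events occurring after drug administration". An unblinded team member gives the drug and the study physician assesses and grades every adverse event. The section also states: "All investigators (study physicians and lab technicians) will be blinded to the treatment allocation".

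**The concern.** A safety control is useful only if it is observed for the same events, in the same way and over the same period as the treated arm. Here the maternal adverse-event interview is started by drug intake, and the control women have no intake during pregnancy. Nausea, pain, bleeding or contractions can occur in pregnancy without any drug. Without control data, a treated-arm event rate cannot be divided into background and drug effect.

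The blinding statement raises a related difficulty. If adverse-event records in pregnancy arise only from post-dose interviews, the existence of a record shows the allocation. The person stated to be blinded is also the person who assesses and grades those records.

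At stake are a stated secondary objective of sub-study B and the accuracy of a blinding claim. The primary objective, the kinetics of CAA, is not touched.

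**Working it through.** The protocol gives no adverse-event rate, power or precision for safety, so there is no figure of its own to reproduce. The check compares the two sections, followed by a short calculation of what a matched comparison could deliver.

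**Comparing the sections**

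| Element | Immediate arm (75) | Delayed arm (25) |
|---|---|---|
| PZQ during pregnancy | yes | no |
| Placebo or sham dose | not applicable | none described |
| Interview at 1 h and 24 h during pregnancy | yes | none described |
| Interview after own PZQ dose | in pregnancy | about 6 months post partum |
| Content stated for days 2, 4, 6 and weekly visits | urine collection | urine collection |
| Delivery, birth-weight, anaemia and infant outcomes | yes | yes |

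1. The adverse-event section speaks of treatment either in pregnancy or after delivery and does not restrict the interviews to one arm. Controls may therefore be interviewed after their own later dose. Such an interview describes a woman who is no longer pregnant, so it cannot serve as a comparison for exposure in pregnancy.
2. Active follow-up is promised for both arms, but the only activity attached to those visits is urine collection. The visit days are counted from PZQ treatment, a starting point that controls do not have during pregnancy.
3. Concurrent maternal adverse-event assessments in pregnancy, as written: 75 treated women and 0 of 25 controls. A difference in rates needs an estimate in each arm, so it cannot be formed.
4. Blinding: drug in one arm, no placebo in the other, and records generated only after the drug. Any such record dated in pregnancy therefore belongs to the immediate arm. Having someone else give the drug does not hide this from the physician who grades the event.

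**Precision if all women were assessed alike**

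Inputs: 75 and 25 women (sub-study B paragraph), and a common event rate p in both arms. The protocol gives no p, so 5%, 10% and 20% are assumptions.

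Half-width of the 95% CI for the difference = 1.96 × √[p(1 − p)(1/75 + 1/25)], with 1/75 + 1/25 = 0.0533.

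- p = 5%: 1.96 × √(0.0475 × 0.0533) = 0.099, about ±10 points
- p = 10%: 1.96 × √(0.09 × 0.0533) = 0.136, about ±14 points
- p = 20%: 1.96 × √(0.16 × 0.0533) = 0.181, about ±18 points

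At p = 5% only 25 × 0.05 = 1.25 control events are expected, so the normal approximation is rough there. These figures show what matched collection would buy. They do not measure the defect, which is that no difference can be estimated at all.

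**The case against.** Four arguments can be made for the plan.

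*Other safety data are compared by arm.* This stands, and it limits the point. A reader might infer that the control arm contributes no safety data. The documents do not support that. The section on recruitment, data and sample collection lists gestational age, newborn anthropometry, Apgar score, maternal bleeding volume and placenta at delivery. Additional outcomes lists maternal anaemia, birth weight, small for gestational age and infant evaluation at 12 and 24 months. The statistical section plans an ANCOVA of the PZQ effect on birth weight. Preterm birth is captured through gestational age. The offspring half of the control arm's safety role is therefore served.

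*The article condenses a fuller protocol.* An event form or visit schedule may exist in the full protocol or in Additional file 1, neither of which is shown. An omission alone would be no finding. Here, however, the article states a safety-control role, a scheme started by drug intake and full physician blinding, and it names the section where the safety details are to be found. These three statements do not fit together as printed.

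*Blinding is not shown to be impossible.* This is correct. The text does not say who conducts the interviews, and a physician could grade masked records if both arms supplied them at matched times. The article describes no such arrangement, so the conflict holds for the scheme as described and not for every possible scheme.

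*The short window should not be exaggerated.* It is tempting to say that 24 hours covers 1 of 42 days of follow-up. Six weeks is a ceiling, because visits stop once both tests are negative, so that ratio does not describe every woman. Nor does the text show what the data safety and monitoring board would receive; it says only that the board reviews sub-study B safety data.

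**Conclusion.** The point holds for maternal adverse events in pregnancy between dosing and delivery. On the text as written these have a treated series of 75 women and no concurrent control series from the 25, although the protocol calls that arm the safety control. The stated blinding of the study physicians conflicts with the same scheme; that of the laboratory technicians does not.

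The conclusion assumes that no placebo, sham contact or matched interview exists beyond what the article describes. If the full protocol contains one, what remains is a matter of wording. The effect is on the secondary objective only. Even with matched collection, a 75 against 25 comparison would be imprecise, at about ±10 to ±18 points under the assumed rates, so it could show large differences and not small ones.

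**What to change.** Reconcile the sub-study B paragraph with the adverse-event section:

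- Use the same adverse-event form in both arms at the same times, counted from randomisation: at 24 h and at the day 2, 4 and 6 visits already set for both groups.
- Put any later collection on a fixed schedule. Do not tie it to the weekly urine visits as they stand. These end at test negativity, so treated women who clear early would be observed for less time than controls who stay positive.
- Record antenatal events such as pregnancy loss up to delivery in both arms. Gestational age at delivery is already recorded.
- Report differences between arms with 95% CIs, and state that precision is low with 75 and 25 women.
- Limit the blinding statement to laboratory readers and any assessor who really is masked. Otherwise describe adverse-event assessment as open-label.

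The cost is a short form at existing early visits, one extra early contact for about 25 controls, any later fixed contacts the team chooses to add, and protocol wording. No dose or treatment timing changes.

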### Additional outcomes

Maternal health outcomes, maternal anaemia (defined as Hb < 11 g/dl) at inclusion and at delivery will be investigated. In offspring, birthweight (with low birthweight defined as weight at birth < 2.5 kg) and small for gestational age (used as an indicator for possible intrauterine growth restriction) will be investigated. In addition, the exposure to PZQ during pregnancy will be evaluated in infants at the age of 12 and 24 months. Time to sit, crawl, stand and walk, incidence of illnesses and vaccine coverage during the follow-up will be recorded.

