**Fig. 1 Fig1:**
[figure not shown]
freeBILy-GABON study outline

**Sub-study A** is a prospective, cross-sectional, observational study conducted in 1000 pregnant women in Lambaréné and surroundings to determine the sensitivity and specificity of the UCP-LF CAA test (index test) for the detection of *S. haematobium* infections in urine samples. Sampling will include standardized urine collection on 3 consecutive days for *S. haematobium* detection by egg microscopy and UCP-LF CAA testing; qPCR and POC-CCA will be done on one urine sample. To control for concomitant parasite infections one stool sample (within the 3 days of urine sampling) will be collected to screen for *S. intercalatum* and soil-transmitted helminths infections, as well as one blood sample will be taken for filaria and *Plasmodia* spp. detection. The blood sample will also be used to measure anti-*Schistosoma* antibodies and to provide blood cell counts and haemoglobin levels. The primary objective of sub-study A is to compare the UCP-LF CAA urine test against a composite diagnostic reference including egg microscopy, qPCR, and serology in order to determine UCP-LF CAA test performance. Sub-study A will allow to identify participants for sub-study B.

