### Sample size calculation

Analysis of the UCP-LF CAA (UCAA*hT*417) test performance will be compared against a composite diagnostic reference (i.e. by latent class analysis). Assuming a 10% egg positivity rate in the study population [32], about 1000 pregnant women should be tested to obtain 100 *Schistosoma* positive women. Assuming further a sensitivity of the index test (UCP-LF CAA) between 80 and 100% with 100 infected women, statistical precision (two-sided 95% confidence limit) of ±7.8% will be achieved if a sensitivity of 80% is observed and a lower limit of 96.4% if a sensitivity of 100% is observed. Due to the limited sensitivity of the egg detection test, to estimate the specificity, only study participants negative for reference tests should be included. Furthermore, assuming a true *Schistosoma* prevalence of 20% (based on a conservative estimate of 50% sensitivity of the egg test) and assuming a false positive rate of 20% of the other two reference tests (PCR and UCP-LF antibody test), at least 500 women will enter the naïve estimate of specificity. This will lead to a statistical precision of between ±3.5 and ± 4.3% depending on the observed specificity. For sub-study B, the analysis is based on the assumption of a non-inferiority delta of 0.10, identical probabilities of positivity and negativity at the end of the sub-study B for both tests (UCP-LF CAA and egg microscopy) and a discordance of 12%, with 100 pregnant women, the power will be 80% to show non-inferiority (type 1 error: 2.5% one-sided).

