### Data management and statistical analysis

All data will be collected on paper forms which will be entered into a REDCap database [59]. Initial data will be double entered in REDCap to ensure their accuracy. Each participant included into the study will receive a unique identifier. The case report from (CRF) is the source documents for personal data, clinical data and laboratory result sheets will be considered as source documents for laboratory results reported in the CRF.

Analysis of the UCP-LF CAA (UCAA*hT*417) test performance will be compared against a composite diagnostic reference by using Latent Class Analysis or other Bayesian approaches which will allow to compare the estimated sensitivity, specificity, positive predictive value (PPV), negative predictive value (NPV) and the accuracy values for detecting *Schistosoma* in the sample. The model will be fitted to determine the Bayesian Information Criteria (BIC), Akaike information Criteria (AIC), the Chi square test and the standardized Residuals.

To assess the effect of PZQ treatment on birth weight, Analysis of covariance (ANCOVA) will be used. This is a fundamental statistical method of analysis for both randomised and non-randomised studies. It is a regression analysis which includes parameter estimates for observed covariates in addition to the treatment effects we are ultimately interested in estimating.

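### The only maternal haemoglobin outcome named is anaemia yes/no at 11 g/dl; adding delivery haemoglobin as a level, adjusted for the inclusion value, would recover power at almost no cost

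*Protocol article*

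**What the plan says.** The section on additional outcomes defines the maternal haemoglobin outcome as a binary status at two times: "maternal anaemia (defined as Hb < 11 g/dl) at inclusion and at delivery will be investigated". The next sentence of that section handles the newborn differently. Birthweight itself is the outcome, and the 2.5 kg limit for low birthweight is added in brackets.

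Under Study design, the sub-study A paragraph says that the inclusion blood sample will also serve "to provide blood cell counts and haemoglobin levels", so a continuous value exists at inclusion. A value at delivery is implied, because anaemia cannot be classified there without one.

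The statistical section names one model for a treatment effect, and only for the newborn: "To assess the effect of PZQ treatment on birth weight, Analysis of covariance (ANCOVA) will be used".

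Sub-study B is a "follow-up study of at least 100 pregnant women identified in sub-study A", with women "randomised 3:1 (75:25) for immediate PZQ treatment during the pregnancy". The delayed group receives PZQ six months after delivery.

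**The concern.** The background section lists maternal anaemia among the harms of schistosomiasis in pregnancy and calls the infection a large contributor to anaemia. At delivery only the immediate arm has been treated, so haemoglobin at that time is a natural randomised contrast of treated and untreated women. The control arm has just 25 women, and a yes/no cut is inefficient in so small a group. A woman who moves from 8 to 10.8 g/dl stays in the anaemic category.

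Haemoglobin also suits ANCOVA better than birth weight does, because it has a pre-treatment value and birth weight has none. As the outcomes are worded, a modest effect of treatment on maternal haemoglobin could go unseen although the data to estimate it are being collected.

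**Working it through.** **The plan's own figure.** The article gives no power, SD, event rate or effect size for haemoglobin or anaemia. Its only power figure for the 100 women of sub-study B concerns the paired comparison of the CAA test with egg microscopy: a "non-inferiority delta of 0.10" and "a discordance of 12%, with 100 pregnant women, the power will be 80% to show non-inferiority (type 1 error: 2.5% one-sided". The large-sample formula gives Φ(0.10·√(100/0.12) − 1.96) = Φ(2.887 − 1.960) = 82.3%, and exact enumeration of the Wald test gives 81.3%. The stated 80% is reproduced, but it says nothing about haemoglobin.

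**Inputs for the haemoglobin check.**
- From the article: arms of 75 and 25, cut at 11 g/dl.
- Assumed: normally distributed haemoglobin; control mean at delivery 10 to 11 g/dl; SD 1.1 to 1.5; inclusion-delivery correlation r of 0.3 to 0.5; treatment shifts the mean by Δ; no losses; two-sided 5% test.

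**Formulas.**
- Yes/no: p_c = Φ((11 − mean)/SD) and p_t = Φ((11 − mean − Δ)/SD), compared with a pooled-variance test of two proportions.
- Unadjusted haemoglobin: power = Φ(Δ/SE − 1.96), with SE = SD·√(1/75 + 1/25) = SD × 0.2309.
- ANCOVA on inclusion haemoglobin: as above, with SD multiplied by √(1 − r²).

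**Central case: mean 10.5, SD 1.3, r = 0.5, Δ = 0.8.**
- Yes/no: p_c = Φ(0.385) = 0.650, p_t = Φ(−0.231) = 0.409, pooled 0.469. The SE under no difference is √(0.469 × 0.531) × 0.2309 = 0.1153. The SE under the alternative is √(0.650 × 0.350/25 + 0.409 × 0.591/75) = 0.1110. Power = Φ((0.241 − 1.96 × 0.1153)/0.1110) = 55%.
- Unadjusted haemoglobin: SE = 0.300, power = Φ(2.665 − 1.960) = 76%.
- ANCOVA: SE = 0.260, power = Φ(3.077 − 1.960) = 87%.

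The same formulas at the central mean, SD and r give:

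| Δ (g/dl) | Anaemia, delayed vs immediate | Yes/no | Unadjusted Hb | ANCOVA | Loss, yes/no vs ANCOVA |
|---|---|---|---|---|---|
| 0.3 | 65% vs 56% | 11% | 17% | 21% | 10 points |
| 0.5 | 65% vs 50% | 25% | 38% | 49% | 24 points |
| 0.8 | 65% vs 41% | 55% | 76% | 87% | 31 points |

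**Simulation check.** Monte Carlo with 75 and 25 women, chi-square against ANCOVA, gave 59%, 76% and 87% for the three analyses at Δ = 0.8, and about 12% against 21% (9 points) for yes/no against ANCOVA at Δ = 0.3. Type I error was close to 5% for each. The proportions formula is slightly pessimistic for the yes/no test, so I rely on the simulation for the ranges.

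**Range over the assumed grid (simulation).**
- Δ = 0.8: about 40–72% with yes/no and 67–95% with ANCOVA.
- Δ = 0.5: about 16–37% and 31–63%.
- The loss at Δ = 0.5 to 0.8 is roughly 10 to 30 points; the extreme corners gave 9 and 34.
- The loss at Δ = 0.3 is about 9 points at central values and 3 to 17 over the grid.

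**How the loss divides.** In the central case at Δ = 0.8 (simulated), 76 − 59 = 17 points come from the cut and 87 − 76 = 11 from baseline adjustment. A separate simulation of this case put logistic regression of anaemia adjusted for inclusion haemoglobin at 65%. Adjustment alone therefore does not make up for the cut.

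**The case against.** The strongest reply is that the article fixes no analysis of this outcome. It says that anaemia will be investigated and gives its definition; it names no test, model or comparison. How an additional outcome is modelled is commonly left to the analysis plan, which is not shown, and a journal article condenses a fuller protocol. Anaemia is also the clinical condition of interest, so defining it by a threshold is legitimate.

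Much of this stands, and it rules out several stronger readings that a reader might infer:
- *That the inclusion value goes unused.* The text says anaemia at inclusion will be investigated, and nothing excludes inclusion haemoglobin as a covariate. The article is only silent on that use.
- *That haemoglobin will be analysed only as yes/no.* The article does not say so. It names no other maternal haemoglobin outcome.
- *That the 75:25 comparison of anaemia is planned.* This is an inference from the sub-study B design. Anaemia at inclusion precedes randomisation and can serve to describe the roughly 1000 women of sub-study A.
- *That the cut costs a fixed 15 to 25 points.* No such figure follows from the documents. It fits the cut alone for standardised effects of about 0.5 to 0.8 (14.5 to 25.6 points with control anaemia of 30 to 70%). It is too high for effects of 0.2 to 0.3 (3 to 10 points), and too low for moderate effects once the baseline is used (29 to 35 points at 0.5 to 0.65 with r = 0.5).

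What the reply does not remove is the outcome definition itself. The section names the measured quantity for birthweight and only the cut for maternal haemoglobin. That is a stated choice of outcome, and improving it needs only values already measured or implied by the outcome.

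**Conclusion.** The point holds as a minor improvement in efficiency. As written, the maternal haemoglobin outcome is a cut at 11 g/dl. If it is compared at delivery between arms of 75 and 25, that cut gives away about 9 points of power for a difference of 0.3 g/dl at central values and about 10 to 30 points for 0.5 to 0.8 g/dl, relative to baseline-adjusted haemoglobin. These figures rest on an assumed mean, SD, correlation and effect, on normality and on no losses. Baseline-adjusted haemoglobin had the higher power throughout the grid; the size of the gain is uncertain. For small effects neither analysis is informative: at 0.3 g/dl, power is about 21% even with ANCOVA in the central case.

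The article makes no power claim for anaemia, and no primary objective is affected.

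**What to change.** Add one sentence to the additional outcomes or to the analysis plan: haemoglobin at delivery is analysed as a continuous additional outcome, by randomised group, using ANCOVA with inclusion haemoglobin and gestational age at enrolment as covariates, and is reported as an adjusted mean difference with its 95% confidence interval. Gestational age is worth including because enrolment spans weeks 16 to 30, so the time from treatment to delivery varies. Keep the proportion with Hb < 11 g/dl in each arm and report it beside the mean difference, so that the clinical threshold stays visible.

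The change needs no new sample or visit, and the method is the one already named for birth weight. The cost is one more analysis of an unpowered additional outcome, which should be labelled as such.
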